### Recruitment {15}

People with type 2 diabetes will be recruited:
From DDI by usual care dieticians, physicians, nurses and trainers.Using advertisements via multiple media outlets that include texts, WhatsApp, flyers, social media and posters. These will target potential participants, primary health care centres and hospitals. Some advertisements will be designed by the public relations team at DDI.

## Assignment of interventions: allocation

### Sequence generation {16a}

Following the baseline assessment, patients will be randomised to the home- or gym-based resistance exercise group or the control group (1:1:1 ratio) using a computer-generated randomisation sequence. Randomisation will be stratified by sex.

### Concealment mechanism {16b}

Blinding of patients and research staff to the interventions is not possible but the staff and patients will be blinded to the sequence and all data will be analysed blind to allocation.

### Implementation {16c}

The allocation sequence will be generated within the electronic database (www.castoredc.com). Patients will be enrolled by a member of the research team.

## Assignment of interventions: blinding

### Who will be blinded {17a}

Blinding of patients and research staff to the interventions is not possible but all data will be analysed blind to allocation.

### Procedure for unblinding if needed {17b}

The current study design is open label with no blinding, and thus, unblinding will not occur.

## Data collection and management

### Plans for assessment and collection of outcomes {18a}

All outcome data will be collected according to developed standard operating procedures.

### Plans to promote participant retention and complete follow-up {18b}

No further strategies, than those described to maintain engagement with intervention, are planned.

### Data management {19}

All data will be kept in a secure storage area with access only to the study staff or on an online database (www.castoredc.com).

### Confidentiality {27}

Access to the collated participants’ data will be restricted to the principal investigator and appropriate research study staff as required. All laboratory samples, completed forms, reports and other records will be identified using a unique participant ID number to maintain participant confidentiality.

### Plans for collection, laboratory evaluation and storage of biological specimens for genetic or molecular analysis in this trial/future use {33}

Blood samples will be collected via venepuncture and analysed in our clinical biochemistry laboratories.

## Statistical methods

### Statistical methods for primary and secondary outcomes {20a}

All statistical analyses will be carried out according to a detailed Statistical Analysis Plan, to be finalised prior to database lock. We will use an intention to treat approach for analysis, using baseline observation carried forward for those who do not attend the 16 weeks visit, and last observation carried forward at the 32 week visit. This will estimate the effect of the interventions. The primary (and secondary) outcomes (all continuous) will be analysed in a hierarchical fashion, first analysing the change in outcome in the gym-based group versus control at 16 weeks at 5% level of significance; this is the group we hypothesise will have the greatest effect size. If this first difference is found to be significant, the home-based group will also be compared to control at the 5% level, and if this is significant, the gym-based group will be compared to the home-based group at the 5% level. The overall type I error will not exceed 5% for each outcome because of the hierarchical nature of the testing. Comparison of the randomised groups at 32 weeks will be conducted in a similar fashion, as a secondary analysis, at the 5% level. As a secondary analysis, we will conduct a per protocol ‘completer’s analyses’ of those who attended at least the 16-week visits (irrespective of their protocol adherence or other characteristics after randomisation). This is a less conservative estimate of the effect of the intervention. Finally, in the per protocol group, we will also investigate the association and correlation of change in HbA1C with change in secondary outcomes.

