#### Primary outcome measure

The primary outcome measure is change in HbA1c from baseline to 32 weeks.

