### Sample size {14}

Previous research has shown that resistance exercise training can result in an ~ 0.6% decrease in HbA1c [12], with a 0.5% in HbA1c also being classified as a clinically relevant change. To detect a 0.5% decrease in HbA1c (standard deviation within groups 0.79%) in the home-based group or gym group versus control, we would require 40 participants per group at 80% power at the 5% significance level. We will recruit 50 to each group to account for drop out.

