### Methods in analysis to handle protocol non-adherence and any statistical methods to handle missing data {20c}

Non-adherence will be handled through the use of intention to treat analysis in the primary analysis. Missing data will be handled by baseline observation carried forward in the primary analysis. Due to the randomised design, multivariable models will not be used to adjust for confounding, and therefore missing covariates will not impact the primary analysis.

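### Carry-forward is fixed as the primary missing-data method; its bias has no guaranteed direction, and its two statements agree only if 16 weeks is the primary time point

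*Protocol article*

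**What the plan says.** Section {20a} of the protocol article sets the intention-to-treat rule as "using baseline observation carried forward for those who do not attend the 16 weeks visit, and last observation carried forward at the 32 week visit" and adds: "This will estimate the effect of the interventions". Section {20c} states the rule again in a shorter form: "Missing data will be handled by baseline observation carried forward in the primary analysis".

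Which visit is primary is not consistent. The outcomes section says "The primary outcome measure is change in HbA1c from baseline to 32 weeks". Section {20a} begins the testing hierarchy elsewhere, "first analysing the change in outcome in the gym-based group versus control at 16 weeks at 5% level of significance", and then says "Comparison of the randomised groups at 32 weeks will be conducted in a similar fashion, as a secondary analysis, at the 5% level".

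The only other handling of missing data in the article is a secondary completer analysis of those who attended at least week 16, which {20a} describes as less conservative. Section {20a} also refers to a separate SAP, which is not shown.

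**The concern.** Baseline observation carried forward (BOCF) enters a change of exactly zero for a person who was not measured. Last observation carried forward (LOCF) enters the week-16 value as if it had been seen at week 32. Either gives the effect in all randomised participants only if the unseen values equal the carried-forward ones on average in each arm, or if the errors happen to cancel between arms. The sentence in {20a} that this estimates the intervention effect is therefore not true in general.

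Two things are at stake. The headline HbA1c difference and its interval would rest on an assumption that the plan does not state. And if the 32-week outcome is primary, the same data could give two different primary results, depending on which section the analyst follows.

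This is a rule the protocol states, not a detail left to the SAP.

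**Working it through.** **Inputs.** From Sample size {14}: "To detect a 0.5% decrease in HbA1c (standard deviation within groups 0.79%) in the home-based group or gym group versus control", 40 per group for 80% power at the 5% level, 50 recruited per group. The dropout rate is not stated; 40/50 = 0.80 implies 20%. Assumed here: two-sided testing, SD of change 0.79, dropout unrelated to outcome, correlation 0.7 between week-16 and week-32 change, and half of dropouts seen at week 16 unless noted.

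**1. The plan's own figure.** n = 2 × (1.96 + 0.842)² × 0.79² / 0.5² ≈ 39.2, so 40 per group. 40/0.80 = 50. Both reproduce.

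**2. BOCF when dropouts would have had the full effect.** With a share d missing in each arm and true effect 0.50:
- Estimate = (1 − d) × 0.50. At d = 0.20 this is 0.40.
- Variance, exercise arm = (1 − d) × 0.79² + d(1 − d) × 0.50² = 0.499 + 0.040 = 0.539. Control arm = 0.499.
- SE = √((0.539 + 0.499)/50) = 0.144.
- SE from the 40 observed per arm = 0.79 × √(2/40) = 0.177. The BOCF SE is about 18% smaller.
- Coverage of 0.50, with bias 0.10 and 0.10/0.144 = 0.694: Φ(1.96 + 0.694) − Φ(−1.96 + 0.694) ≈ 0.89.

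| Missing per arm | BOCF estimate | BOCF SE | Observed-only SE | BOCF coverage of 0.50 |
|---|---|---|---|---|
| 10% | 0.45 | 0.151 | 0.167 | 94% |
| 20% | 0.40 | 0.144 | 0.177 | 89% |
| 30% | 0.35 | 0.136 | 0.189 | 80% |

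A simulation of 20,000 trials at 20% missing agreed: mean 0.401, average SE 0.144, sampling SD 0.145, coverage 89%. Power was 79% for BOCF and 80% for observed cases.

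**3. BOCF when dropouts gain nothing.** The all-randomised effect is 0.80 × 0.50 + 0.20 × 0 = 0.40. BOCF recovers it; a missing-at-random analysis would return about 0.50.

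**4. LOCF at week 32, 20% missing, true week-32 effect 0.50.**
- Constant effect: 0.80 × 0.50 + 0.10 × 0.50 = 0.45.
- Week-16 effect half as large: 0.40 + 0.10 × 0.25 = 0.425.
- Effect waning from 0.70 to 0.50, all dropouts seen at week 16: 0.40 + 0.20 × 0.70 = 0.54, an overstatement.

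**5. Unequal dropout with a common drift, no true effect, BOCF.** Take an assumed rise of 0.3 in both arms.
- Dropout 30% gym, 10% control: 0.70 × 0.3 − 0.90 × 0.3 = −0.06, favouring exercise. Simulated type I error is about 7%.
- Rates swapped: 0.27 − 0.21 = +0.06, against exercise.
- Equal dropout and no drift: type I error about 5%.

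**6. The two sections side by side, week-32 analysis.**

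| Participant | {20a} | {20c}, if 32 weeks is primary |
|---|---|---|
| Missed both visits | Baseline | Baseline |
| Seen at week 16, missed week 32 | Week-16 value | Baseline |

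If 16 weeks is primary, both sections say baseline for a missed week-16 visit and there is no conflict.

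**The case against.** The strongest defence is that the significance test is hardly affected. In the base case the ratio of estimate to SE is 0.40/0.144 = 2.78 under BOCF and 0.50/0.177 = 2.82 from observed cases. The BOCF SE matches that estimator's own sampling variation, and type I error is about 5% with equal dropout and no drift. A reader might infer that the standard error is wrong or the test invalid; neither follows. What stands is narrower: the interval is tighter than the observed data support for a 0.50 effect, and it is centred elsewhere if dropouts would have benefited.

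Second, shrinkage from 0.50 to 0.40 is not a fact about this trial. It assumes that those who leave would have kept the full benefit, which cannot be checked here. This objection stands in full.

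Third, a reader might infer that carry-forward is likely to manufacture a benefit for exercise. The documents do not support that. They give no HbA1c drift, and reminders go only to the exercise groups ({11c}), with nothing added in {18b}: "No further strategies, than those described to maintain engagement with intervention, are planned". If that affects retention at all, it suggests more loss among controls. With upward drift, that biases against exercise.

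Fourth, {20a} and {20c} can be read consistently if 16 weeks is primary. That is correct, but this reading contradicts the stated primary outcome, so the time-point conflict has to be resolved either way.

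Finally, the unseen SAP may add sensitivity analyses. That would help, but it would not change the primary rule the protocol states.

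**Conclusion.** The concern holds in a limited form. Carry-forward single imputation is the stated primary method, and it estimates the intervention effect only under a strong, unstated assumption. At the implied 20% dropout, BOCF gives about 0.40 for a true 0.50 (0.45 to 0.35 for 10% to 30% dropout), with about 89% interval coverage, provided dropouts would have had the same effect. If they gain nothing, 0.40 is correct for all randomised participants. LOCF can overstate a waning effect, and unequal dropout with drift can bias either way. It would therefore be wrong to say that the method always shrinks the effect, or that it is reliably conservative.

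The disagreement between {20a} and {20c} is real if the 32-week outcome is primary and disappears if 16 weeks is. It follows from the unresolved primary time point.

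This should be corrected before the SAP is finalised. It does not by itself invalidate the primary test. The dropout pattern, correlation, drift and effect trajectories are assumptions; the 0.5%, 0.79%, 40 and 50 come from the protocol.

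**What to change.** 1. Reconcile the primary time point between the primary outcome statement and {20a}.
2. State one missing-data rule in both {20a} and {20c}: a likelihood-based repeated-measures model of HbA1c at baseline, 16 and 32 weeks in all randomised participants, with arm-by-visit terms, or equivalent multiple imputation. These measurements are already scheduled for everyone ({12}), and the order of the hierarchical tests need not change.
3. Add a delta-adjusted or control-based imputation as a sensitivity analysis, to cover dropouts who lose the benefit.
4. Keep BOCF/LOCF at most as a labelled sensitivity analysis, and replace the claim in {20a} with a statement of the assumption the chosen method makes.

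The cost is revised wording, slightly more analysis work and somewhat wider intervals: in the worked case, an SE of about 0.177 if only observed week-32 values inform it, rather than 0.144. No extra data collection is needed. Because {20a} says the SAP will be finalised before database lock, the change could still be pre-specified if that point has not passed.

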## Discussion

The current trial is a single-centre, three-arm randomised controlled trail. It has been designed to test the effectiveness of home- and gym-based resistance exercise training over a period of 32 weeks in people with type 2 diabetes. It is known that resistance exercise training can effectively reduce HbA1c in people with type 2 diabetes [12] and the current study will answer whether delivery of such an intervention without regular supervision and outside of a gym-based facility is also effective, potentially allowing a more pragmatic delivery of resistance exercise within clinical practice.

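### The primary time point is contradictory: the primary outcome is HbA1c change to 32 weeks, but the testing hierarchy starts at 16 weeks and makes 32 weeks secondary

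*Protocol article*

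**What the plan says.** The section Primary outcome measure is unambiguous: "The primary outcome measure is change in HbA1c from baseline to 32 weeks". The Discussion describes the trial as a test of "home- and gym-based resistance exercise training over a period of 32 weeks".

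The section Statistical methods for primary and secondary outcomes {20a} sets a fixed order of tests for the primary and secondary outcomes. It begins by "first analysing the change in outcome in the gym-based group versus control at 16 weeks at 5% level of significance". Home versus control and then gym versus home follow, each only if the preceding test is significant. The section then adds: "Comparison of the randomised groups at 32 weeks will be conducted in a similar fashion, as a secondary analysis, at the 5% level". On error control it says: "The overall type I error will not exceed 5% for each outcome because of the hierarchical nature of the testing".

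Two other statements depend on which visit is primary.

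- **Missing data.** Section {20a} specifies "using baseline observation carried forward for those who do not attend the 16 weeks visit, and last observation carried forward at the 32 week visit". Section {20c} says: "Missing data will be handled by baseline observation carried forward in the primary analysis".
- **Sample size {14}.** The calculation is framed as: "To detect a 0.5% decrease in HbA1c (standard deviation within groups 0.79%) in the home-based group or gym group versus control". It gives no time point for the effect or the standard deviation.

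**The concern.** The outcome definition and the analysis section give different answers to the same question: on which visit does the trial's main conclusion rest? Under the outcome definition it is 32 weeks. Under {20a} it is 16 weeks, because the gatekeeping sequence starts there and 32 weeks is expressly secondary.

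The practical difficulty comes if the visits disagree. If gym training beats control at 16 weeks but not at 32, {20a} calls the trial positive and the outcome definition calls it negative. The reverse pattern reverses the verdicts. A reader of the final report could not tell which verdict had been fixed in advance.

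The error-control statement is affected too. HbA1c passes through two complete hierarchies, each opened at 5%, and the 32-week one is not made conditional on the 16-week one. The ordering therefore protects the 5% level within a visit, not across the two.

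**Working it through.** **1. The statements side by side**

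| Section | What it implies about the primary visit |
|---|---|
| Primary outcome measure | 32 weeks, explicitly |
| Discussion | 32 weeks as the period of training; weaker support |
| Statistical methods {20a}, test order | 16 weeks tested first; 32 weeks secondary |
| Statistical methods {20a}, missing data | Baseline carried forward at 16 weeks; last observation carried forward at 32 weeks |
| Missing data {20c} | Baseline carried forward in the primary analysis, which matches the 16-week rule |
| Sample size {14} | No time point |

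This is not a slip in a single word. Section {20a} carries 16 weeks through the test order and the labelling of 32 weeks, and {20c} fits that reading. The outcome definition is equally plain on the other side.

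**2. The plan's own sample size**

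Inputs from {14}: difference 0.5%, within-group SD 0.79%, 80% power, 5% significance. Two-sided testing is assumed, since sidedness is not stated.

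n per group = 2 × (1.960 + 0.842)² × 0.79² / 0.5² = 2 × 7.85 × 0.6241 / 0.25 ≈ 39.2, rounded up to 40.

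This reproduces the stated 40. A one-sided test would need 31, so two-sided is the reading that fits. Power at 40 per group is 80.8% by the normal formula and 79.8% by the t-test. With 20% dropout (the rate implied by 40 and 50, not stated), 40 / 0.80 = 50. The figure is right for one pairwise comparison at one visit, but it does not show which visit.

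**3. Error if either visit could be claimed**

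When no arm differs from another, any rejection within a hierarchy requires its first test, gym versus control, to reject. The chance of at least one false claim over the two visits is therefore

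1 − P(|Z₁₆| ≤ 1.96 and |Z₃₂| ≤ 1.96),

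with the two statistics bivariate normal with correlation r. The document gives no correlation, so r is an assumption.

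| Assumed r | Chance of at least one false positive |
|---|---|
| 0 (independent) | 1 − 0.95² = 9.75% |
| 0.5 | 9.1% |
| 0.7 | 8.3% (0.0835) |
| 0.8 | 7.8% |
| 0.9 | 7.0% |

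Two changes measured on the same patients from the same baseline should be clearly correlated, so 0.5 to 0.9 is used as the working range: 9.1% down to 7.0%.

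**4. Effect on the missing-data rule**

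Consider a participant seen at 16 weeks and absent at 32. Under {20a} the 32-week change is the 16-week change carried forward. Under {20c}, if 32 weeks is primary, the change is zero. For someone who misses both visits the two rules agree. So moving the primary test to 32 weeks without editing {20c} would leave a second contradiction, affecting those lost between the visits.

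**5. Sample size after the fix**

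With the whole 5% spent at one visit, step 2 is unchanged: 40 per group, 50 with dropout. Keeping both visits as primary at 2.5% each would need 48 per group before dropout, or 48 / 0.80 = 60 recruited.

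**The case against.** The strongest reply is that {20a}, read alone, is a coherent plan. It names one ordered sequence at 16 weeks and labels 32 weeks secondary. A reader might infer that the protocol declares two primary tests; it does not. The conflict appears only when {20a} is set against the outcome definition. That corrects how the problem is described but does not remove it.

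A reader might also take 7.0% to 9.1% as the trial's actual type I error. The documents do not support that. Neither section allows success at either visit: each names one visit, and they name different ones. The inflation arises only if the ambiguity is used as a choice.

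Nor do the documents show that the visit will be picked after both results are known. Section {20a} requires a statistical analysis plan to be finalised before database lock, and {16b} and {17a} say the data will be analysed blind to allocation. These are real safeguards but only partial ones: {17b} describes the trial as open label, and 16-week data will exist before lock. Nor is this a detail properly left to the analysis plan, whose author would have to overrule one of two statements the protocol already makes.

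Finally, three-set training runs over weeks 9–32, so by week 16 only 8 of its 24 weeks have been delivered. One might conclude that 16 weeks is an invalid assessment time. The document gives no time-course basis for that, and the point here does not rely on it. The Discussion's mention of 32 weeks can likewise be read as intervention length alone.

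**Conclusion.** The contradiction is real, unreconciled and needs correcting. It rests on the text and on no numerical assumption: the declared primary outcome is assigned to a secondary analysis, and discordant results at 16 and 32 weeks would have no agreed interpretation.

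The numerical consequence is conditional. If success could be claimed at either visit, the false-positive chance for gym versus control would be about 7.0% to 9.1%, given assumed correlations of 0.9 to 0.5 and a null effect at both visits. The stated 5% limit for each outcome would then hold only within one time point.

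The sample size is not in error. What is missing is the visit to which its inputs belong.

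**What to change.** 1. In {20a}, run the hierarchy (gym versus control, home versus control, gym versus home) on the HbA1c change from baseline to 32 weeks as the sole primary analysis, in line with the outcome definition. Make the 16-week comparisons secondary, without a separate confirmatory claim.
2. Reword the type I error statement so that it refers to the 32-week hierarchy.
3. Reconcile the missing-data rule for the primary analysis: {20c} gives baseline observation carried forward, whereas {20a} gives last observation carried forward at 32 weeks. One rule should be stated in both places.
4. In {14}, state the time point to which the 0.5% effect and 0.79% SD apply. The investigators should first confirm that both hold at 32 weeks; the document does not show this, so it should not simply be asserted.

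The cost is wording in the protocol, carried into the analysis plan and completed before database lock. Under {25}, the amendment needs local ethics committee approval. No extra participants or visits are needed, and 40 per group (50 with dropout) stands.

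### Making gym versus home wait for a significant home-versus-control result is not needed to hold type I error at 5%, and it costs power for that comparison

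*Protocol article*

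**What the plan says.** Statistical methods {20a} sets out a three-step order for the primary and secondary outcomes:

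1. "first analysing the change in outcome in the gym-based group versus control at 16 weeks at 5% level of significance". Gym goes first because "this is the group we hypothesise will have the greatest effect size".
2. "If this first difference is found to be significant, the home-based group will also be compared to control at the 5% level".
3. "if this is significant, the gym-based group will be compared to the home-based group at the 5% level".

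The reason given is error control: "The overall type I error will not exceed 5% for each outcome because of the hierarchical nature of the testing". No other reason is given for making step 3 depend on step 2. The 32-week comparison follows the same pattern as a secondary analysis.

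Sample size {14} is built on comparisons with control only: "To detect a 0.5% decrease in HbA1c (standard deviation within groups 0.79%) in the home-based group or gym group versus control". The stated need is 40 per arm, for 80% power with 5% tests. The section adds: "We will recruit 50 to each group to account for drop out".

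**The concern.** The gym-versus-home comparison can be made formally only when home has already beaten control. If gym training works and home training does not, or works too weakly to reach significance, the sequence stops with one significant and one non-significant comparison against control. That pair of results is not a valid test that the two programmes differ, and the direct test that would be valid has been ruled out in advance.

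Such a restriction is justified if it buys error control. The question is whether it does. If it does not, the trial gives up power for a comparison that the investigators chose to place in the error-controlled family and gets nothing in return. The same applies to every secondary outcome and to the 32-week analysis.

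**Working it through.** **Inputs from the protocol.** Difference 0.5 percentage points of HbA1c, within-group SD 0.79, 40 per group needed, 50 recruited, 80% power, 5% level (Sample size {14}); 1:1:1 allocation (Sequence generation {16a}); 5% at each step (Statistical methods {20a}). Sidedness is not stated.

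**Reproducing the plan's figure.** n per group = 2 × (1.96 + 0.8416)² × 0.79² / 0.5² = 2 × 7.849 × 0.6241 / 0.25 = 39.2, rounded up to 40. A one-sided test would need only 31, so the plan is two-sided. The two-sample t-test at n = 40 has power 79.8%. Recruiting 50 corresponds to 20% drop-out (40 / 0.8 = 50). The stated figure is reproduced.

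**Is the last condition needed?** Write G, H and C for the true mean changes. Any two of G = C, H = C and G = H imply the third. Under the relaxed rule (test G versus C at 5%; if significant, test H versus C and G versus H, each at 5%):

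- All three nulls true: any false claim needs a rejection at step 1, so the probability is at most 5%.
- Only G = C true: step 1 is the only place an error can occur, so at most 5%.
- G = C false: H = C and G = H cannot both be true. At most one true null remains and it is tested at 5%, so at most 5%.

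The relaxed rule therefore controls the error by itself. The first condition is still required: with no conditions at all, the chance of a false claim when all arms are equal is 12.2%.

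**Simulation check** (normal data, SD 0.79, n = 40 per arm, two-sided t-tests). Chance of any false rejection under the relaxed rule:

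| True reductions | Relaxed rule |
|---|---|
| All arms equal | 5.0% |
| Gym 0.5, home = control | 3.4% |
| Gym = home = 0.5 | 3.4% |
| Gym = control, home 0.5 | 5.0% |
| Gym very far from control, home equal to control or to gym | 5.0% |

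In the third row the written rule gives 1.9%. The relaxed rule spends error that the written rule leaves unused, and stays within 5%.

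**What the last condition costs.** Chance of a significant gym-versus-home result. As written, all three tests must be significant; relaxed, gym versus control and gym versus home must be. The pairs of true effects are assumptions. The documents supply about 0.6 (earlier research) and 0.5 (design difference), and no separate value for home.

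| Gym reduction | Home reduction | As written | Relaxed |
|---|---|---|---|
| 0.5 | 0 | 2% | 68% |
| 0.6 | 0.2 | 7% | 59% |
| 0.6 | 0.4 | 7% | 20% |
| 0.6 | 0.5 | 4% | 8% |

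In the first row gym versus control is significant in about 80% of trials, and in about 96% of those the last condition then blocks gym versus home. With 50 per arm analysed, that row becomes 3% against 80%. The gym-versus-control and home-versus-control steps are identical under both rules, so neither loses power.

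**The case against.** The other side has a good deal in its favour.

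- **The protocol says nothing false.** A fixed sequence does hold the error at 5% per outcome. A reader might infer from this point that the type I error statement is wrong; it is correct as written.
- **Gym versus home is not an objective.** Objectives {7} asks whether each programme lowers HbA1c relative to control, and Sample size {14} is set on the same comparisons. The Discussion asks whether home delivery works, which home versus control answers.
- **The order has a rationale.** How much benefit home training gives up relative to the gym is of most interest once home training has been shown to work.
- **The large losses need a weak home arm.** A reader might infer that the protocol expects home training to fail. It does not: it hypothesises that both programmes work and says only that gym should have the largest effect. With home at 0.4 or 0.5 against gym at 0.6, gym versus home is poorly powered under either rule.
- **Estimation is not barred.** Nothing stops the investigators reporting the gym-home difference with a confidence interval, so readers would not be forced to compare two p-values.

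All of this stands as a limit on importance. It does not rescue the condition itself. A priority order usually trades power between comparisons, but here nothing is gained for the two comparisons with control. A confidence interval does not restore the confirmatory test. An analysis plan that kept the protocol's rule would keep the loss.

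**Conclusion.** The point holds as an inefficiency in a valid procedure. The condition linking gym versus home to home versus control adds no protection that 5% control requires, and it reduces power for gym versus home. The loss ranges from small (4% against 8% when the two programmes are close) to almost total (2% against 68% when home has no effect). These figures rest on SD 0.79, 40 analysed per arm, normal data, two-sided 5% tests and assumed home effects. The logical argument needs none of the assumed effects; it needs only three arms, pairwise nulls, and each test valid at 5%.

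Priority is modest. The comparison ranks third in the sequence and lies outside the primary aim and the sample-size basis. No error rate, sample size or primary-aim conclusion is affected.

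**What to change.** Keep gym versus control as the first step and replace the last step with: *If gym versus control is significant at 5%, home versus control and gym versus home will each be tested at the 5% level.* Add one line of justification: if gym truly differs from control, at most one of the two remaining null hypotheses can be true, so the error stays at or below 5%. Apply the rule separately to each outcome and each time point, and fix it in the protocol and the statistical analysis plan before database lock.

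The cost is a sentence or two. It needs no extra participants, data or alpha, and takes no power from either comparison with control. The first condition must not be dropped along with the second. Adopting the rule does not make the trial powered for gym versus home when the two effects are close.

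### The 5% per-outcome error guarantee covers one testing sequence only, yet the same outcome is tested again at 32 weeks at a further full 5%, and the protocol disagrees with itself on which time point is primary

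*Protocol article*

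**What the plan says.** Protocol article, Statistical methods for primary and secondary outcomes {20a}, sets out a three-step sequence for each outcome:

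- Step 1: "first analysing the change in outcome in the gym-based group versus control at 16 weeks at 5% level of significance".
- Step 2: "If this first difference is found to be significant, the home-based group will also be compared to control at the 5% level".
- Step 3: "if this is significant, the gym-based group will be compared to the home-based group at the 5% level".

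The error statement follows at once: "The overall type I error will not exceed 5% for each outcome because of the hierarchical nature of the testing". The next sentence adds the later visit: "Comparison of the randomised groups at 32 weeks will be conducted in a similar fashion, as a secondary analysis, at the 5% level". Nothing in the section makes the 32-week sequence conditional on the 16-week one or divides the 5% between them.

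The section headed Primary outcome measure gives a different priority: "The primary outcome measure is change in HbA1c from baseline to 32 weeks". Sample size {14} plans on a 0.5% HbA1c difference with SD 0.79% and names no visit: "we would require 40 participants per group at 80% power at the 5% significance level".

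**The concern.** A fixed sequence protects against multiple comparisons because a later test is made only if every earlier one succeeded. Here that protection works within a visit. The 32-week sequence starts afresh, so each outcome has two ungated openings at a full 5%. The guarantee is worded as overall and per outcome, and each outcome is assessed at both visits.

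This would matter less if it were clear which sequence carries the trial's conclusion. It is not. The sequence attached to the 5% statement is at 16 weeks, while the declared primary outcome is at 32 weeks, in the analysis labelled secondary. A report could cite the statistical methods section for a 16-week success or the outcomes section for a 32-week success, each at nominal 5%. What is at stake is the error rate behind the HbA1c claim, including the home-versus-control comparison, which is the trial's new question.

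**Working it through.** **Inputs from the protocol.** Each step at 5%, a separate 5% at 32 weeks, and no gate between visits ({20a}); difference 0.5%, SD 0.79%, 40 per group required and 50 recruited ({14}); 1:1:1 allocation ({16a}).

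**Assumptions.** Two-sided tests, since the sides are not stated. A correlation r between the 16- and 32-week test statistics, which the protocol does not give; I take 0 to 0.95.

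**Check of sidedness.** n per group = 2(1.960 + 0.842)² × 0.79² / 0.5² = 39.2, rounded up to 40. This reproduces the plan. A one-sided 5% test would need 31, so two-sided 5% is the natural reading.

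**One sequence (the plan's own figure).** Under no effect anywhere, a false claim requires step 1 to reject, which has probability 5%. If gym works strongly and home does nothing, the first false claim possible is at step 2, again 5%. If both arms work equally, only step 3 is a true null; simulation with 50 per arm and effects of 0.5 gives about 2.6%. The stated 5% limit therefore reproduces for a single visit.

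**Two ungated sequences, no effect.** A false claim occurs if step 1 rejects at either visit:

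error = 1 − P(|Z16| < 1.96 and |Z32| < 1.96), with (Z16, Z32) bivariate normal with correlation r.

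| r (assumed) | P(neither rejects) | Per-outcome error |
|---|---|---|
| 0 | 0.9025 | 9.75% |
| 0.5 | 0.9093 | 9.1% |
| 0.7 | 0.9165 | 8.4% |
| 0.8 | 0.9219 | 7.8% |
| 0.9 | 0.9296 | 7.0% |
| 0.95 | 0.9354 | 6.5% |

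The r = 0 row is 1 − 0.95². The upper bound at any correlation is 5% + 5% = 10%. Simulation of the full three-step sequences at both visits agrees: about 9.1%, 8.4% and 7.0% at r = 0.5, 0.7 and 0.9.

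**Two ungated sequences, other truths** (simulation, 50 per arm, the same effect at both visits):

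| Truth | r = 0.5 | r = 0.7 | r = 0.9 |
|---|---|---|---|
| Gym effect 1.0, home none | 9.1% | 8.4% | 7.0% |
| Gym effect 0.5, home none | about 7% | 6.4% | 5.5% |
| Both effects 0.5 | 4.9% | 4.6% | 3.9% |

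So the excess is not confined to the case where nothing works, but it disappears if both arms work equally at the planned effect.

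**The case against.** A reader might infer that the 5% sentence is simply false. The text does not support that. The sentence comes directly after the three 16-week comparisons and before 32 weeks is mentioned, and for that sequence it is correct. A secondary analysis at nominal 5% does not inflate the error of a primary family, and whether the two visits form one family is a choice rather than a fact. This part of the objection stands. It falls short of an answer because the protocol itself defines the primary outcome at 32 weeks, so the secondary label cannot be relied on to keep that visit outside the confirmatory claim.

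A reader might also infer that the two openings are independent, or that the problem remains whichever visit is made primary. Neither follows. The tests use the same participants and baseline, and carrying the last value forward to 32 weeks tends to raise the correlation and shrink the excess, although it stays above 5% for any correlation below 1. Once one visit is fixed as primary and the statement is limited to it, 5% holds.

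Finally, the trial hypothesises that both interventions work, and with equal 0.5 effects the combined error is below 5%. That is true, but a guarantee of a maximum error rate has to cover the null cases as well.

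**Conclusion.** The point holds in a limited form. The hierarchy secures 5% per outcome at one time point. Across both time points it does not: under no effect the rate is about 7.0% to 9.1% for r from 0.9 to 0.5, with a ceiling of 10%. These figures assume two-sided tests, approximate normality and a correlation that the protocol does not supply. They apply only if both sequences can support a claim, and the conflict between the outcomes section and the statistical methods section leaves that open. The inflation is moderate and the remedy is wording, but the protocol states an explicit error limit for its primary outcome and should state one that it meets.

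**What to change.** Reconcile Primary outcome measure with {20a} so that one time point is primary; under the outcome definition that is 32 weeks. Run the three-step hierarchy there, and limit the 5% statement to that sequence. Report the other time point as estimates with 95% confidence intervals, with no controlled significance claim. This needs no extra participants or data. The cost is that the other time point can no longer support a stand-alone claim of significance.

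Do not instead place the second time point after gym versus home in one long chain. If both arms have the planned 0.5 effect, gym versus home is a true null, and the chain passes it in only about 2.6% of trials with 50 per arm (1.8% with 40), so the second time point would almost never be tested.

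Splitting alpha equally between the visits would also restore 5%, but at a price: at 2.5%, 2(2.241 + 0.842)² × 0.79² / 0.5² = 47.5, so 48 per group would be needed in place of 40.
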